# Robot-assisted gait training for improved gait independence in individuals with acute hemiparetic stroke: study protocol for a randomized controlled pilot trial

**DOI:** 10.1186/s40814-025-01694-6

**Published:** 2025-08-29

**Keywords:** Cerebrovascular disease, Gait ability, Rehabilitation, Robotics, Stroke, Stroke rehabilitation, Walking, Feasibility studies, Randomized controlled trials as topic

## Abstract

**Background:**

Robot-assisted gait training (RAGT) has proven effective in addressing gait disorders in patients with stroke. However, its efficacy in patients with acute stroke has not yet been demonstrated. This pilot study is designed to evaluate the following: (1) feasibility of conducting a randomized controlled trial on RAGT for enhancing gait postacute stroke and (2) to obtain preliminary estimates regarding the potential efficacy of RAGT for achieving gait independence during the acute phase.

**Methods:**

We will conduct an assessor-blinded, single-center, randomized controlled pilot trial involving 32 patients with acute stroke who are unable to walk. Participants will be randomly assigned to either the RAGT or the conventional gait training (CGT) groups. Each participant will receive 180 min of daily rehabilitation, including 60 min dedicated to gait training. The RAGT group will receive 40 min of RAGT and 20 min of CGT, while the CGT group will engage in 60 min of CGT. Interventions will continue for up to 8 weeks, or until participants achieve gait independence, as indicated by a Functional Ambulation Category score of ≥ 3. Feasibility outcomes will include recruitment, enrollment, protocol adherence, and retention rates. The primary clinical outcome will be the incidence of achieving gait independence during the intervention period. Secondary clinical outcomes will include gait performance measures, assessments of physical function and activity, and intervention dose. Adverse events associated with RAGT and CGT will also be documented to evaluate the safety of both interventions.

**Discussion:**

Implementing RAGT during the acute phase of stroke may facilitate earlier attainment of gait independence compared to CGT. We aim to provide valuable insights into the feasibility of the proposed study design and generate preliminary data on the potential effects of RAGT on gait independence in the acute phase of stroke, providing a framework for future larger-scale trials.

**Trial registration:**

This clinical trial was registered with the Japan Clinical Trials Registry (jRCT) on 19 June 2023 (registration number: jRCTs042230040). The study protocol was initially registered as version 1.0 and has since undergone minor amendments—currently on version 4.0. This protocol was written based on the latest version (ver. 4.0) registered with jRCT.

## Background

Stroke is a major cause of physical dysfunction and gait disorders [1, 2]. Gait disorders limit activities of daily living and social participation [3]. The percentage of individuals recovering their gait ability post-stroke is estimated to be 41–85% [4]. Therefore, enhancing gait function in stroke survivors is an important goal of rehabilitation therapy [5].

Recent literature has increasingly reported the efficacy of robot-assisted gait training (RAGT) in individuals with stroke. A systematic review and meta-analysis indicated that RAGT, when combined with conventional physical therapy (CGT), significantly improved gait independence in individuals who were unable to walk within 3 months of stroke onset [6], leading to its inclusion in several guidelines [7, 8]. The efficacy of RAGT for individuals with hemiparetic stroke is attributed to the robotic control mechanism, which facilitates intensive repetitive training and task-oriented training by providing partial or full body weight support and assistance with movement [9].

However, the optimal timing for initiating RAGT remains unclear. Most studies evaluating the efficacy of RAGT have focused on individuals with stroke in the subacute phase. The aforementioned systematic review and meta-analysis concentrated on randomized controlled trials involving participants 2–8 weeks following stroke onset [6]. Other systematic reviews have consistently demonstrated the efficacy of RAGT in enhancing gait ability in individuals within the first 3 months post-stroke, yet they did not include randomized controlled trials conducted during the first week post-stroke [10–12]. Further research is required to determine the appropriate timing for implementing RAGT [13].

We defined the “acute” phase as the period occurring within 7 days of stroke onset [14] and have planned a study to clarify the efficacy of RAGT initiated during this timeframe. We hypothesize that the initiation of RAGT in the acute phase would enable individuals to achieve gait independence more rapidly than with CGT. Early RAGT promotes motor learning and mitigates disuse by delivering high-intensity, task-oriented gait training from an early stage [9, 15]. To test this hypothesis, we aim to examine the following: (i) the feasibility of conducting a randomized controlled trial on RAGT for improving gait after acute stroke and (ii) obtaining preliminary estimates of the potential efficacy of RAGT for achieving gait independence during the acute phase.

## Methods

### Study design and setting

This study is an assessor-blinded, single-center, randomized controlled pilot trial following the Consolidated Standards of Reporting Trials (CONSORT) extension for pilot trials [16]. A flowchart of the study is illustrated in Fig. 1. Individuals with stroke will be enrolled and randomly assigned to either the RAGT group or the CGT group. The study will be conducted at Fujita Health University Hospital, Aichi, Japan. In accordance with the Declaration of Helsinki of 1964 (revised in 2013), written informed consent will be obtained from all participants (or their kin or legal guardians if the participants are unable to provide consent) prior to participation. This study received approval from the Fujita Health University Institutional Review Board (Approval No. CR24-031) and is registered in the Japan Registry of Clinical Trials (jRCTs042230040).

**Fig. 1 Fig1:**
[figure not shown]
Study flowchart

### Participants

The inclusion criteria are as follows: (i) individuals aged 16–90 years, (ii) those with hemiplegia due to a first-ever supratentorial cerebral infarction or hemorrhage, (iii) those starting intervention within 7 days of stroke onset, (iv) those with severe lower extremity hemiparesis at the preintervention assessment (total score of ≤ 6 on the Stroke Impairment Assessment Set [SIAS] [17–19] motor items for lower extremities), (v) those with severe gait disorder at the preintervention assessment (score of ≤ 1 on the Functional Ambulation Categories [FAC] [20, 21]), (vi) those with sustained awareness at the preintervention assessment (eye opening score of 4 and motor response score of 6 on the Glasgow Coma Scale [GCS] [22, 23]), (vii) those with body weight of 35–100 kg, and (viii) those with height of 140–190 cm.

The exclusion criteria are as follows: (i) individuals with a history of stroke (except for individuals with no symptoms despite imaging findings indicating a history of stroke); (ii) those with pre-existing gait disorders due to neuromuscular or musculoskeletal diseases; (iii) those that participated in other interventional studies related to lower limb/trunk motor function and gait; (iv) those with a history of epileptic seizures within the past 2 years (including seizures caused by the current stroke); (v) those with cardiovascular or respiratory diseases that impede exercise therapy; (vi) those with uncontrolled hypertension; (vii) those with osteoporosis of the lower limbs or spine; (viii) those with heterotopic ossification in the lower extremities leading to limited range of joint motion; (ix) pregnant women or those with possibility of pregnancy; (x) those with infectious diseases requiring isolation; (xi) those with urinary or fecal incontinence that may compromise the robotic device through contamination; (xii) those unable to wear the robotic leg due to overweight, deformities in lower limbs, or pressure ulcers; and (xiii) individuals deemed unsuitable by the attending physician, principal investigator, or research assistants.

### Recruitment

Potential participants will be identified from patients admitted to the Fujita Health University Hospital Emergency Center. Prescreening of potential participants will be conducted by trained physical and occupational therapists, and eligibility will be carefully assessed by a rehabilitation physician based on the prescreening results.

### Randomization

Participants will be stratified by stroke type and randomly allocated to either the RAGT or CGT group using a computer-generated permuted block randomization method with permuted block sizes of two and four. Random allocation will be performed by an independent researcher not involved in the assessments, using the Research Electronic Data Capture tool [24].

### Interventions

The study schedule is illustrated in Fig. 2. Participants will undergo the intervention during their hospitalization at Fujita Health University Hospital. The intervention will continue until participants achieve an FAC score of ≥ 3 or for up to 8 weeks from the start of training. Participants in both the RAGT and CGT groups will receive rehabilitation for 180 min per day, 7 days per week. Both groups will undergo gait training for 60 min per day [30] and non-gait training for 120 min per day. The RAGT group will undergo RAGT for 40 min per day and CGT for 20 min per day, for 6 days a week, with an additional 60 min of CGT once per week. The CGT group will undergo CGT for 60 min, 7 days per week (Fig. 2).

**Fig. 2 Fig2:**
[figure not shown]
Intervention protocol. The intervention will be conducted 7 days a week until the Functional Ambulation Category score is ≥ 3 or until 8 weeks from the start of training. The participants will receive 180 min of rehabilitation per day. The daily gait training for both groups will last 60 min, and the remaining 120 min of rehabilitation will comprise other training (excluding gait training). In the robot-assisted gait training (RAGT) group, 40 min of RAGT and 20 min of conventional gait training (CGT) will be provided 6 days a week (days of RAGT and CGT), and 60 min of CGT will be provided once a week (in principle, only CGT will be provided on Sundays). In the CGT group, patients will receive 60 min of CGT for 7 days a week

The following medical devices and therapies are prohibited during the intervention period: medical devices, such as electrical, magnetic, and shock wave stimulators for the lower limbs; other devices for improving gait and balance; vibration stimulators; virtual reality devices; augmented reality devices; mixed reality devices; therapies such as mirror therapy or constraint-induced movement therapy for the lower limbs.

### Robotic device

The Welwalk (Toyota Motor Corporation, Aichi, Japan), which was developed to support gait training in individuals with hemiparetic stroke, will be used for RAGT (Fig. 3). A multi-center randomized controlled study has reported that RAGT, using Welwalk, is effective in improving gait independence in individuals with subacute cerebral infarction [25]. Several single-center randomized controlled studies have similarly reported improvements in gait independence through RAGT with Welwalk in individuals with subacute stroke [26, 27]. The device consists of a low-floor treadmill, knee-ankle-foot orthosis-type robot, safety suspension system (used for body weight support), robot weight support device, front monitor for patients, and monitor and control panel for the therapist. The knee-ankle-foot orthosis-type robot is equipped with a load sensor on the sole that detects the gait cycle based on the load. The knee joint motor assists in knee joint flexion during the swing phase and extension during the stance phase. Therapists will set the degree of robotic assistance as low as possible to avoid complicating gait mechanics significantly while still allowing for compensatory movements. Furthermore, therapists will provide minimal support or guidance as needed.

**Fig. 3 Fig3:**
[figure not shown]
Overview of the Welwalk device

### Outcomes

#### Feasibility assessment

Following prior recommendations [28], we will assess the feasibility of this pilot study based on the following indicators: (i) recruitment and enrollment rates, defined as the average number of participants enrolled in the study per month; (ii) enrollment rate, defined as the proportion of individuals who consent to participate among those who meet the eligibility criteria during the preintervention assessment; (iii) adherence rate, defined as the proportion of participants who complete the intervention according to the schedule, serving as an indicator of the intervention’s acceptability; and (iv) retention rate, defined as the proportion of participants who complete outcome measures from baseline to predischarge assessment.

These measures will serve as progression criteria to determine whether to proceed with the study [29]. The specific criteria are as follows: (i) recruitment rate of at least 0.8 participants per month; (ii) enrollment rate of at least 90% of screened eligible individuals consenting to participate [30]; (iii) adherence rate, with at least 90% of participants completing scheduled training times [30]; and (iv) retention rate, with a minimum of 90% of enrolled participants completing all outcome measures until follow-up [30, 31]. Recruitment rate criteria were established based on our institution’s experience, while enrollment, adherence, and retention rates were determined with reference to similar previous studies on RAGT [30, 31]. Even if a participant fails to meet any of the four established criteria, the study will proceed with protocol modifications if the underlying issues can be addressed [29].

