**Fig. 4 Fig4:**
[figure not shown]
SPIRIT figure Note: * Items to be assessed if the Functional Ambulation Category score is ≥3. SIAS, Stroke impairment assessment set

The primary clinical outcome measures will include the number of days from the baseline assessment to the achievement of gait independence and the percentage of individuals achieving gait independence—operationally defined as an FAC score ≥ 3. In particular, this primary clinical outcome represents the most promising candidate for future clinical trial endpoints. Secondary clinical outcomes encompass gait parameters as assessed by velocity, stride length, and cadence in the 10-m walk test; 6-min walk distance; SIAS scores for lower limb motor and trunk function; total score on the Functional Independence Measure (FIM); and the number of steps taken during gait training during the intervention period. The FAC is a reliable and validated clinical measure of gait ability based on the amount of assistance needed [20, 21]. The 10-m walk test is a reliable and validated clinical measure of walking ability [33, 34], whereas the 6-min walk test is a reliable and validated clinical measure of motor endurance [35, 36]. The number of steps taken during gait training will be recorded manually by a therapist using a counting device. The SIAS serves as a reliable and validated index for assessing functional impairment in patients with stroke [17–19]. It accounts for motor function, tension, sensory function, range of motion, pain, trunk function, higher brain function, and muscle strength on the non-paralyzed side, with total scores ranging 0–72. The total score for SIAS motor items is calculated as the sum of the hip flexion, knee extension, and foot pat tests, with scores ranging 0–15 points. The FIM, which comprises 13 motor items and 5 cognitive items, is a proven reliable index for assessing independence in activities of daily living [37, 38]. Each item is rated on a scale of 1–7, with scores of 1–4 indicating the need for varying levels of physical assistance, a score of 5 indicating the need for supervision, a score of 6 indicating modified independence, and a score of 7 indicating complete independence. The FIM cognitive total is the sum of scores of the five cognitive items, ranging 5–35 points.

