### Sample size

This is a pilot study; therefore, the sample size was not calculated based on statistical testing power [16]. We aim to enroll 32 participants, as this is presumed to be an adequate sample size for gathering insights on recruitment, enrollment, adherence, and retention rates. With 32 participants recruited, a retention of 90% can be estimated to within a 95% confidence interval (CI) ranging from 75–96%. This sample size should also suffice to accurately assess means and variances [42] and to provide data regarding clinical outcomes.

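### The adherence criterion, meant to show the intervention's acceptability, can be met with only 13 of 16 RAGT participants adherent, and retention is defined in two conflicting ways

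*Protocol article*

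**What the plan says.** The Feasibility assessment section lists four indicators and then four matching progression criteria.

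- **Adherence, indicator:** "adherence rate, defined as the proportion of participants who complete the intervention according to the schedule". The same sentence says the rate serves to indicate how acceptable the intervention is.
- **Adherence, criterion:** "adherence rate, with at least 90% of participants completing scheduled training times".
- **Retention, indicator:** "retention rate, defined as the proportion of participants who complete outcome measures from baseline to predischarge assessment".
- **Retention, criterion:** "a minimum of 90% of enrolled participants completing all outcome measures until follow-up".

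Neither adherence sentence names an arm. Analytical methods promises the four rates with 95% confidence intervals and does not mention rates by arm. Under Clinical outcomes, the fixed assessments are at 4 weeks, 8 weeks and discharge. The Discussion acknowledges that there is no long-term follow-up. The Fig. 4 note marks some measures as "Items to be assessed if the Functional Ambulation Category score is" at least 3. The Feasibility assessment section ends by saying that a missed criterion leads to a modified protocol if the cause can be dealt with.

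**The concern.** The question for the next trial is whether patients within a week of stroke tolerate the robotic training. About half of the participants never receive it. If they adhere well to conventional training, they raise the pooled rate and can carry the criterion over 90% while RAGT falls short. A missed criterion prompts a look at the cause, but a met one does not, so a false pass would go unexamined. The Discussion says the findings may be used to refine intervention parameters to improve adherence, and a pooled rate cannot show which arm needs it.

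The retention problem is different. Two sentences in one section give different endpoints and different sets of measures, so the observed rate, and whether it reaches 90%, may depend on which sentence is applied.

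**Working it through.** **Inputs.** The Sample size section gives the total: "We aim to enroll 32 participants". The Randomization section describes a "computer-generated permuted block randomization method with permuted block sizes of two and four". The ratio is not stated. I assume 1:1, so 16 per arm; stratification by stroke type could shift this slightly. True adherence by arm is not given anywhere, so the rates below are assumptions shown as a range.

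**The plan's own figure.** The Sample size section gives a 95% CI of 75% to 96% for 90% retention with n = 32. The Wilson interval is [p + z²/2n ± z√(p(1−p)/n + z²/4n²)] / (1 + z²/n). With p = 0.90, n = 32 and z = 1.96:
- centre (0.900 + 0.060)/1.120 = 0.857
- half-width 1.96 × √(0.002813 + 0.000938)/1.120 = 0.107
- interval 75.0% to 96.4%

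The stated figure is reproduced. The finding concerns definitions, not this arithmetic.

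**Step 1: what the pooled rule needs.** 0.90 × 32 = 28.8, so 29/32 = 90.6% passes and 28/32 = 87.5% fails.

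**Step 2: the lowest RAGT result that still passes.** With CGT at 16/16, RAGT needs 29 − 16 = 13, and 13/16 = 81.3%. The Wilson interval for 13/16 is 57.0% to 93.4%.

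**Step 3: how often the pooled rule passes.** Let A ~ Bin(16, p_R) and B ~ Bin(16, p_C), independent. Then P(pass) = Σ P(B = b) × P(A ≥ 29 − b). For p_R = 0.80 and p_C = 0.98:

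0.7238 × 0.5981 + 0.2363 × 0.3518 + 0.0362 × 0.1407 + 0.0034 × 0.0281 = 0.521.

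| True RAGT | True CGT | P(pooled rule passes) | P(passes and RAGT below 15/16) | P(RAGT ≥ 15/16) |
|---|---|---|---|---|
| 75% | 98% | 0.342 | 0.279 | 0.063 |
| 80% | 95% | 0.415 | 0.280 | 0.141 |
| 80% | 98% | 0.521 | 0.381 | 0.141 |
| 80% | 100% | 0.598 | 0.457 | 0.141 |
| 85% | 98% | 0.715 | 0.432 | 0.284 |

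**Step 4: what a RAGT-only 90% rule would cost.** 0.90 × 16 = 14.4, so 15/16 = 93.8% is needed, because 14/16 = 87.5%. P(Bin(16, p) ≥ 15) = 16p¹⁵(1−p) + p¹⁶.
- p = 0.90: 0.329 + 0.185 = 0.515
- p = 0.95: 0.371 + 0.440 = 0.811

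For comparison, with both arms at 90% the pooled rule passes with probability P(Bin(32, 0.90) ≥ 29) = 0.600.

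**Step 5: the two retention sentences side by side.**

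| | Indicator | Criterion |
|---|---|---|
| Endpoint | predischarge assessment | follow-up |
| Measures | outcome measures, not further specified | all outcome measures |
| Match with the schedule | fits, as discharge is the last assessment named | no assessment is called follow-up |

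Neither sentence says how measures that depend on the FAC score count for a participant below 3. The indicator also leaves open whether someone discharged before week 8 still owes the 8-week assessment. Discharge times are not given, so I cannot size this effect.

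**The case against.** The best defence of pooling is that the stated objective is the feasibility of a randomised trial. Control-arm adherence to daily training then matters too. RAGT tolerance is also visible elsewhere: intervention dose is compared between groups, adverse events are recorded for both interventions, and dropouts are recorded with reasons and stage. Rates by arm are ordinary content for an analysis plan that is not shown. This is fair, and pooling is inferred from the lack of a named arm, not stated outright. What remains is that the text gives the adherence rate a specific purpose, acceptability of the intervention, and sets a threshold that does not isolate it. The other data would inform a reader but do not enter the criterion.

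On retention, it can be said that follow-up is loose wording for the last assessment. That is probably what is meant, but a progression criterion should not need the guess.

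A reader might infer three stronger points that the documents do not support:

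- **One missed session makes a participant non-adherent.** Both adherence phrases can be read that way, but neither says so, and a tolerance may sit in the full protocol.
- **Retention must fail even with no dropouts**, because some participants never reach FAC 3. The Fig. 4 note suggests those items are simply not due below 3, and the figure that identifies them is not shown. The recovery range of 41–85% in the Background describes gait ability after stroke in general, so it cannot be used to cap completion in this severely affected group.
- **A missed criterion ends the programme.** The section expressly allows proceeding with modifications.

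**Conclusion.** The concern holds for the adherence criterion as worded and for the mismatch between the retention sentences. The adherence criterion can be met with RAGT adherence at 13/16 (81%). Under the assumed 80% RAGT and 98% CGT adherence it is met about 52% of the time, and about 34% to 72% of the time as true RAGT adherence runs from 75% to 85%. These figures rest on 16 per arm, independent participants and assumed adherence rates; the 13/16 example needs only the 16 per arm. The retention conflict is textual and carries no number. Because a miss leads to modification, the practical harm is a false pass on adherence and a retention result that two readers could report differently. This is a modest defect in a stated decision rule, and it is cheap to remove.

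**What to change.** **Adherence.** Report the rate by arm with 95% CIs, base the acceptability judgement on the RAGT arm, and show CGT beside it. Do not simply move the 90% to 16 participants without comment. That rule means 15/16, and it would turn away a truly 90%-adherent arm about 49% of the time (1 − 0.515) and a 95%-adherent arm about 19% of the time (1 − 0.811). Either state the required count out of 16 or say that the observed rate will be read with its interval.

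**Retention.** Use one definition in both sentences: the proportion of enrolled participants who complete all assessments scheduled for them from baseline to the predischarge assessment. Count FAC-conditional items as not applicable when FAC is below 3, and report by arm. State whether the 8-week assessment is due after an earlier discharge. Keep the secondary measures in the definition; reducing it to FAC alone would change what is being measured.

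**Cost.** Two criteria are reworded, and no new data are needed. The price is precision: the Wilson interval for 15/16 is 72% to 99%, against 76% to 97% for 29/32.
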